## Abstract

**Background:**

In the Netherlands, the first adolescents with diabetes mellitus type 2 as a result of obesity have recently been diagnosed. Therefore, it is very important that programs aiming at the prevention of type 2 diabetes of obese adolescents are developed and evaluated.

**Methods:**

Go4it is a multidisciplinary group treatment that focuses on: 1) increasing awareness of the current dietary and physical activity behaviour (i.e. energy balance behaviour), 2) improving diet, 3) decreasing sedentary behaviour, 4) increasing levels of physical activity, and 5) coping with difficult situations. Go4it consists of 7 sessions with an interval of 2–3 weeks.

The effectiveness of the multidisciplinary group treatment compared with usual care (i.e. referral to a dietician) was evaluated in a randomised controlled trial. We examined effects on BMI(sds), body composition, energy expenditure, glucose tolerance and insulin resistance (primary outcome measure), as well as dietary and physical activity behaviour and quality of life. An economic evaluation from a societal perspective was conducted alongside the randomised trial to evaluate the cost-effectiveness of the multidisciplinary treatment program vs. usual care.

**Discussion:**

In this paper we described a multidisciplinary treatment program (Go4it) for obese adolescents and the design of a randomised controlled trial and economic evaluation to evaluate its effectiveness and cost-effectiveness.

**Trial registration:**

Netherlands Trial Register (ISRCTN27626398).

## Background

Overweight and obesity in childhood are associated with negative psychosocial factors, orthopaedic complications, an increased risk for diseases such as hypertension, dyslipidaemia, asthma, sleep-apnoea and a strong increase of impaired glucose tolerance [1,2]. Impaired glucose tolerance precedes the onset of type 2 diabetes mellitus [3]. Overweight children are likely to remain overweight and are at increased risk of becoming obese compared to children of normal weight [4].

Sinha and co-workers found impaired glucose tolerance in 21% of obese children and 25% of obese adolescents [3]. Four percent of these obese adolescents had type 2 diabetes. At the paediatric outpatient clinic of the VU University Medical Center, glucose-intolerance and insulin-resistance was diagnosed in 18% and 52% of obese adolescents, respectively [5]. In 2003, the last Dutch national surveillance system of diabetes in children reported the first children with type 2 diabetes as a result of obesity.

Several reviews on interventions for treating obesity in children have been produced recently. These reviews suggest that there is some evidence that treatment of obesity in children and adolescents is feasible. However, there is a limited amount of data on effective components of programs to treat childhood obesity [6-10]. Cognitive behavioural modification techniques have shown promising results regarding lifestyle changes in obese children [11]. For obese adolescents the impact of an intensive intervention programme aimed at attaining a healthy lifestyle has not yet been evaluated. The prevalence of obesity in the Netherlands is, analogous to the United States, expected to increase in the coming years [12]. Therefore, there is an urgent need for interventions aimed at the prevention of obesity among adolescents as well as effective therapeutic interventions aimed at a healthy weight of the already obese.

For this reason, we developed Go4it, an intervention program for obese adolescents. This paper describes the design of the Go4it study, a randomised controlled trial (RCT) with an economic evaluation alongside. The aim of this study is to investigate the effectiveness and cost-effectiveness of this multidisciplinary group treatment for obese adolescents.

## Methods

### Design

The effectiveness of Go4it will be evaluated in a randomised controlled trial with an economic evaluation alongside. The Medical Ethics Committee of VU University Medical Center approved the study protocol.

### Intervention

Go4it is a multidisciplinary group treatment for obese children that is based on the programmes of Braet et al [11], Epstein et al [13] and the materials of the Dutch Obesity Intervention in Teenagers (DOiT) [11,14]. During 7 sessions with an interval of 2–3 weeks the adolescents received education on dietary behaviour, physical activity and energy balance. They also received cognitive behavioural therapy in which they were learned how to improve their lifestyle regarding a healthy weight and how to maintain an adequate energy balance. Go4it was carried out multidisciplinary in an outpatient clinic with a dietician, paediatrician/endocrinologist and psychologist involved. The first session was focussed on increasing awareness of the current lifestyle. Besides dietary and activity journals, step counters (pedometers) were used to increase awareness of the actual behaviour. Next, the adolescents had to set goals with respect to improving their energy balance behaviour. Additionally cognitive-behavioural therapy characteristics were used, e.g. learning to cope with difficult situations (parties, holidays) and teasing. Go4it works with homework tasks and the education is interactive. After 6, 14, 26, and 36 weeks, booster group sessions were scheduled in order to encourage the adolescents to maintain or further improve their energy balance behaviour and to discuss possible problems or questions. In addition, two separate sessions for the parents were organised. These parental sessions consisted of education concerning the health risks of overweight, healthy physical activity and dietary behaviour and how to support their children. Special materials were developed for this program; an information book, a workbook, and a dietary and activity diary. In addition, specific worksheets for every session were developed. The control group received the current regular care, consisting of referral to a dietician in the home care setting.

### Study population

#### Recruitment of the study population

All adolescents with overweight or obesity in the age range of 12–18 years who were referred to the outpatient paediatric obesity clinic of the VU University Medical Center were asked to participate. Overweight and obesity were defined according to the Cole criteria [15]. A paediatrician interviewed all adolescents concerning past medical history, weight development, anthropometrics, socio-economic status (SES) of the parents, and ethnicity. Additionally the following three questionnaires were administered as part of the regular care of the obesity clinic. The adolescents and their parents also received an information brochure about the study. Within two weeks, we phoned them to ask for their willingness to participate. Written informed consent was obtained from all adolescents as well as their parents.

#### Child Behaviour Checklist *(filled in by parents)*

The Child Behaviour Checklist (CBCL) is a questionnaire assigning quantitative scores to behaviour problems and competences of children and adolescents at 4 to 18 years of age. The CBCL was filled out by parents or other caregivers. It is composed of 20 competence items and 118 behaviour problem items grouped into four competence scales and eleven problem scales. The competence scales include: activities (amount and quality of participation in sports, hobbies, games as well as jobs and chores), social (number and quality of relationships with others and involvement in organizations), school (an index of competence in school) and total competence score obtained summing the activities, social and school scales (a global index of adaptive functioning). The problem scales include eight syndrome scales: withdrawal, somatic complaints, social problems, anxiety/depression, thought problems, attention problems, delinquent behaviour, and aggressive behaviour; two psychopathology scales, internalizing and externalizing and, lastly, a total problem score, an overall index of the reported problems [16,17].

#### Youth Self-Report *(filled in by the adolescents)*

The Youth Self Report (YSR) provides self-ratings for the same competence and problem items as those of the CBCL. The YSR also includes open-ended responses to items covering physical problems, concerns, and strengths. The adolescents rate themselves for how true each item is now or was within the past six months, using the same three-point response scale as the CBCL [16,18,19].

#### Child Eating Disorder Examination-questionnaire

The Child Eating Disorder Examination Questionnaire (ChEDE-Q)measures three forms of overeating: objective bulimic episodes, subjective bulimic episodes and objective overeating episodes. The ChEDE-Q also measures four methods of weight control: self-induced vomiting, laxative misuse, diuretic misuse and intense exercising [20]. The items of the ChEDE-Q are derived from the initial eating disorder examination interview [21]. The ChEDE-Q was modified to make it suitable for use in populations of Dutch children and is more concrete and simpler for children.

#### Inclusion and exclusion criteria

Adolescents are eligible when they meet the following inclusion criteria: 1) age between 12–18 years; 2) overweight or obesity according the definition of Cole et al [15]. Exclusion criteria for the study are: not Dutch-speaking, overweight/obesity as a result of a known syndrome or organic cause (hypothyroidism), mental retardation, physical limitations and diagnosed Diabetes Mellitus type 2.

### Randomisation procedure

All participants will be randomly assigned to the intervention or control group, using SPSS for a random selection of a sample. Randomisation was stratified by age group (12–14 y, 15–18 y) and gender. Randomisation took place after the baseline measurements.

### Sample size calculation

The sample size calculation is based on a difference in BMIsds of 0.29 (10%) between the intervention and control group after 18 months. The standard deviation for this BMIsds is considered to be 0.5. Based on these data, in an intention-to-treat analysis, 43 subjects per group are needed to detect this difference in mean BMIsds with an alpha of .05 and a power of .80. A sample of 108 persons (n = 54 per group) is required taking into account a dropout rate of 25% [5,11].

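### The printed inputs need 47–48 subjects per group for 80% power, not 43; with 43 per group, two-sided power is about 76%

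*Protocol article*

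**What the plan says.** All the inputs stand in one paragraph of the Protocol article, under Sample size calculation. The target is given as "The sample size calculation is based on a difference in BMIsds of 0.29 (10%) between the intervention and control group after 18 months". On variability: "The standard deviation for this BMIsds is considered to be 0.5". The result follows directly and is said to rest on those data: "43 subjects per group are needed to detect this difference in mean BMIsds with an alpha of .05 and a power of .80". The section does not say whether alpha is one- or two-sided. It mentions no baseline correlation and no gain from repeated measurements.

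The Measurements section names BMI(sds) as the primary outcome, measured at baseline, 6 and 18 months. The Statistical analyses section plans longitudinal regression adjusted for baseline values, with 95% confidence intervals for the group difference. The sample size paragraph does not refer to that adjustment.

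**The concern.** The paragraph gives everything needed for the standard two-group calculation of a difference in means, and the usual formula does not return 43. A gap of 4 to 5 per group, about 10%, is too large to come from choosing the normal or the t distribution, or from rounding up to a whole subject.

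This calculation supports the primary outcome. A reader faced with a null result would take it to come from a trial with an 80% chance of detecting 0.29. On the printed assumptions, the chance of missing that difference with 43 per group is nearer one in four than one in five.

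**Working it through.** **Inputs, all from Sample size calculation:** difference Δ = 0.29; SD σ = 0.5; α = 0.05; power 0.80; equal groups; stated n = 43 per group. The standardised difference is 0.29 / 0.5 = 0.58.

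**Step 1. Try to reproduce 43 with a two-sided test.**

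n = 2 (z₀.₉₇₅ + z₀.₈₀)² σ² / Δ² = 2 × (1.960 + 0.842)² × 0.5² / 0.29² = 46.66, so **47 per group**.

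The two-sample t-test (noncentral t) gives 47.64, so **48 per group**. Neither is 43.

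**Step 2. Try one-sided α = 0.05.** The same formula with 1.645 in place of 1.960 gives 36.8, so 37. The t-test gives 37.5, so 38. The stated 43 lies between the one-sided and two-sided answers and matches neither.

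**Step 3. Power at 43 per group, two-sided.**

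Normal: Φ(0.58 × √(43/2) − 1.960) = Φ(2.689 − 1.960) = Φ(0.729) = **76.7%**.

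t-test: **75.8%**, a type II error of 24.2%.

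**Step 4. Difference detectable with 80% power at 43 per group.**

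Normal: 0.5 × (1.960 + 0.842) × √(2/43) = 0.302. t-test: **0.306**. Both exceed 0.29.

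**Step 5. What would return 43?** Each of these is an input that the paragraph does not print.

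| Unprinted change | Value needed for n = 43, 80% power, two-sided |
|---|---|
| Smaller SD | about 0.480 (normal) or 0.474–0.475 (t-test) |
| Larger difference | 0.302 (normal) or 0.306 (t-test) |
| Baseline correlation ρ, with variance multiplied by 1 − ρ² | 0.28 (normal) or 0.32 (t-test) |
| Lower power, inputs as printed | 0.76 |

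For the correlation row, the normal version is ρ = √(1 − 43/46.66) = 0.28. The t-test version is ρ = √(1 − (0.29/0.3056)²) = 0.316.

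**Step 6. Could rounding of the printed difference explain it?** Taking 0.295, the upper limit of what rounds to 0.29, still needs 46 (normal) or 47 (t-test).

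**The case against.** Four points can be made for the plan.

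*Sidedness is not stated.* At one-sided 0.05, 43 per group gives 84.7% (t-test) or 85.2% (normal), above 80%. So the shortfall in power depends on a two-sided reading. That is correct, but two-sided is the usual default and fits the 95% confidence intervals in Statistical analyses. The one-sided reading does not produce 43 either.

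*The SD may have been rounded.* An SD of 0.475–0.48 prints as 0.5 and returns 43. This is plausible for a condensed article and cannot be settled without the cited sources. Even so, the text prints 0.5 and ties the result to it. Rounding could also go the other way: an SD just under 0.55 needs about 57 per group.

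*The planned analysis is baseline-adjusted.* This is the strongest point. The 76% belongs to an unadjusted comparison at 18 months. If 0.5 is the unadjusted SD, a correlation of about 0.32 restores 80%, and an assumed correlation of 0.5 would give about 87%. The true power of the planned analysis may therefore reach or exceed 80%. But the calculation claims no such gain. If 0.5 is already the SD of change or of the adjusted outcome, the argument fails.

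*The gap is small.* It is 3 to 4 power points. It affects neither the type I error nor any estimate, and a null result would also be read from its confidence interval. This limits the consequence but does not make the printed figure right.

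**Conclusion.** The point holds. On the printed inputs, 43 per group does not follow from 80% power under either sidedness. For a two-sided, unadjusted comparison at 18 months, the requirement is 47–48 per group. With 43, power is 75.8–76.7% and the detectable difference is about 0.306 by the t-test.

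This conclusion takes the difference as 0.29, the SD as 0.5 and the test as two-sided. It does not show that the baseline-adjusted analysis has less than 80% power, because that depends on a correlation the article does not give. It shows that the stated power is not supported by the assumptions offered for it. The shortfall is modest, but it concerns the primary outcome.

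**What to change.** Reword the sample size paragraph in one of two ways, stating the sidedness of alpha in either case.

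- **(a) Keep the unadjusted calculation.** Say that 43 analysed per group gives about 76% power for a difference of 0.29, or 80% power for about 0.31.
- **(b) Base the calculation on the planned analysis.** Redo it for the baseline-adjusted comparison and print the assumed baseline-to-18-month correlation with its source. If 0.5 is the unadjusted SD, a correlation of at least 0.32 makes 43 sufficient. If 0.5 is already the SD of change, this route is closed and (a) applies.

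If the calculation actually used a less rounded SD, print that value.

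The cost is one paragraph: either the stated power becomes slightly less favourable, or one assumption becomes explicit. No more participants are needed, and neither conduct nor analysis changes.

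Both options concern the number analysed. The step from 43 to 54 per group for 25% dropout is a separate matter and should be checked in the same edit: 43 × 1.25 = 53.75, whereas 43 / 0.75 = 57.3, so 58.

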### Statistical analyses

Descriptive statistics (means ± SD, or median and interquartile ranges, as appropriate) will be used to describe the study sample with regard to baseline characteristics. To evaluate the effects of the intervention, longitudinal linear and logistic regression analysis will be used. The mean difference between intervention and control group with 95%-confidence intervals will be calculated. Regression analyses will be adjusted for baseline values and possible confounders such as gender and age. Also effect modification will be investigated using interaction terms between intervention group and gender and age, respectively. All analyses will be performed according to the intention-to-treat-principle, meaning that we will not impute values for missing data [36].

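### Recruiting 54 per group does not leave the plan's own 43 after 25% dropout: it leaves 40.5, and 58 per group would be needed

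*Protocol article*

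**What the plan says.** All the figures are in the article's Methods, under Sample size calculation. The target difference is given thus: "The sample size calculation is based on a difference in BMIsds of 0.29 (10%) between the intervention and control group after 18 months". On variability: "The standard deviation for this BMIsds is considered to be 0.5". The error rates are set "with an alpha of .05 and a power of .80", without saying whether alpha is one- or two-sided. From these the article concludes that "43 subjects per group are needed to detect this difference in mean BMIsds". The allowance for losses follows at once: "A sample of 108 persons (n = 54 per group) is required taking into account a dropout rate of 25" per cent. No inflation formula is shown.

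Two other sections bear on the point. Measurements schedules data collection at baseline, 6 months and 18 months. Statistical analyses plans longitudinal regression adjusted for baseline values and says that "we will not impute values for missing data".

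**The concern.** A dropout allowance has one job: after the expected loss, the required number must still be there. So the number to recruit is the required number divided by the proportion retained. Here the recruited number, the dropout rate and the required number are all printed in the same paragraph, and the first two do not yield the third.

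At stake is how the trial's size is described for its primary outcome, BMIsds. A reader is told that 108 participants secure 80% power after a 25% loss. If dropout runs exactly as expected, the head count at 18 months falls short of the article's own requirement, and a null result would be read against a power that the printed inputs do not deliver.

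**Working it through.** **Inputs, all from Sample size calculation:** difference 0.29; SD 0.5; alpha 0.05 (taken as two-sided, an assumption); power 0.80; 43 per group required; 25% dropout; 54 per group (108 in total) recruited.

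**1. Reproducing the plan's 54.**
- Multiplying by one plus the dropout rate: 43 × 1.25 = 53.75, rounded up to 54. This matches.
- Dividing by the proportion retained: 43/(1 − 0.25) = 57.33, rounded up to 58. This does not match.
- Dividing by 0.80, as for 20% dropout: 43/0.80 = 53.75, again 54. This matches, but for a different dropout rate from the one stated.

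**2. What 54 per group leaves.**
- After 25% loss: 54 × 0.75 = 40.5 per group, 81 in total, against 43 per group, 86 in total.
- Loss that 54 can absorb while keeping 43: 1 − 43/54 = 20.4%.
- With 58 recruited: 58 × 0.75 = 43.5, which meets 43. That is 4 more per group and 8 more in total (116 against 108).

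**3. Power cost of the dropout step alone.** Two-sample, two-sided t-test with standardised difference 0.29/0.5 = 0.58.

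| Per group | Power |
|---|---|
| 40 | 72.6% |
| 40.5 | 73.2% |
| 41 | 73.7% |
| 43 | 75.8% |
| 48 | 80.3% |

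From 43 to 40.5 the loss is 75.8 − 73.2 = 2.6 points. If 43 is instead taken at face value as giving 80%, the standardised difference it implies is 0.611, and 40.5 per group then gives 77.5%, a loss of 2.5 points. Either way the step costs about 2.5 points.

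**4. Separating the base figure.** With 0.29, SD 0.5, two-sided 0.05 and 80% power, the t-test needs 47.6, so 48 per group (normal approximation 46.7, so 47). One-sided, the figures are 38 and 37. None is 43. Of the 6.8-point gap between 80% and 73.2%, about 4.2 points (80 − 75.8) belong to the base figure and about 2.6 to the dropout step.

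**5. Quantities for a restatement at 40.5 per group.**
- An 80% power t-test needs a standardised difference of 0.630, so the detectable difference is 0.630 × 0.5 = 0.315.
- If 0.5 is the unadjusted SD and the analysis adjusts for a baseline with correlation r, the residual SD is 0.5 × √(1 − r²). Setting 0.29/(0.5 × √(1 − r²)) = 0.630 gives √(1 − r²) = 0.58/0.630 = 0.920, so r is about 0.39.

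**The case against.** Four points can be made on the other side.

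First, the planned analysis is not an unadjusted t-test at 18 months. It is longitudinal and adjusts for baseline, and a baseline correlation of about 0.39 would restore 80% power at 40.5 per group. This stands as a reason not to claim that the trial is underpowered in fact. It does not rescue the printed calculation, which states one difference and one SD and takes no credit for a baseline correlation or for repeated measurements.

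Second, a reader might infer from the no-imputation statement that everyone who drops out adds nothing to the 18-month comparison. The documents do not support that. With a 6-month visit and a longitudinal model, a participant lost after 6 months can still contribute the 6-month value, and in a likelihood-based model that value also informs the 18-month estimate. How much depends on the model form and the timing of dropout, which the article does not give.

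Third, a reader might attribute the whole fall from 80% to about 73% to the dropout allowance. That is wrong: most of it is already present at 43 per group.

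Fourth, multiplication by 1.25 is an inference, since no formula is printed and 43/0.80 gives the same 53.75. This is fair, but the mismatch does not depend on how 54 was reached: 54 × 0.75 is below 43 in any case.

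**Conclusion.** The sample size paragraph contradicts itself. With the stated 25% dropout, 54 per group leaves 40.5, which is 2.5 short of the stated 43. Keeping 43 needs 58 per group, and 54 covers a loss of about 20%. Nothing elsewhere in the article repairs this, and it is not rounding.

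The consequence is modest: about 2.5 points of power, assuming a two-sided test, the stated difference and SD, and no gain from baseline adjustment or 6-month data. The absolute figure of about 73% also carries the separate problem that the stated inputs lead to 48 rather than 43, so it should not be read as the effect of the dropout step. Whether the planned analysis would in practice fall below 80% cannot be settled from the article, because it gives no baseline correlation and does not say whether 0.5 is an unadjusted SD. The paragraph should be corrected; no estimand, test or decision rule is affected.

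**What to change.** Replace the last sentence of the sample size paragraph with one of the following.

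- State that 108 randomised with 25% dropout leaves 40 to 41 per group at 18 months, which gives about 73% unadjusted power for 0.29 at SD 0.5, or 80% power for a difference of 0.315. Say that the 73% also reflects the base figure.
- Or state that 54 per group tolerates about 20% dropout, not 25%, if 43 per group are to remain. This repairs the dropout step only and leaves the derivation of 43 to be corrected separately.
- Or state the baseline correlation on which the adjusted analysis relies for 80% power: at least about 0.39 at 40.5 per group, if 0.5 is the unadjusted SD.

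Each costs one sentence and needs no extra enrolment. The price is a less favourable stated power or tolerated dropout, or an explicit assumption that the paragraph does not now make.
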